##### Multiple-Comparison Correction

For voxel-wise analyses, statistical inference will be performed with the following corrections. At the voxel level, uncorrected *P*<.001 will be used as an initial threshold. At the cluster level, familywise error (FWE) correction (*P*<.05) will be applied to control for multiple comparisons across the brain. In parallel, FDR correction will be applied where appropriate to control the expected proportion of false positives. For independent component analysis–based network analyses, dual regression outputs will be thresholded using FWE correction (*P*<.05). This combination ensures robust control of type I error.

##### Power Analysis

A priori power analysis was conducted using G*Power (version 3.1) and the fMRIPower toolbox. On the basis of pilot data and prior studies of similar paradigms, an expected effect size of Cohen *d*=0.6 (moderate) was used. For a voxel-level threshold of *P*<.001, uncorrected and cluster-level FWE of *P*<.05, and a sample size of 30 per group, the analysis achieves >80% power to detect activation differences in relevant cortical regions. This power analysis informed our sample size and statistical thresholds.

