This study is structured as an exploratory randomized controlled clinical trial, with participants allocated in a 1:1 ratio to the intervention and control groups, matched for age and sex to comprehensively assess and evaluate the neurophysiological and holistic health effects of the *marsha nasya karma* procedure in comparison to a control group (Figure 1). Settings of the study include NARIP and AIMS.

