### Sample Size

As this is designed as an exploratory study aiming to gather preliminary data on the neurophysiological effects of the *nasya karma* procedure and its impact on various health parameters, a sample size of 60 (30 per group) is considered appropriate to achieve the study objectives and provide valuable insights that will inform the design of future, larger-scale clinical trials. Feasibility is a critical consideration as recruiting a larger sample of participants willing to undergo both the *nasya karma* procedure and twice-repeated fMRI assessments may be challenging, particularly among healthy volunteers. However, the expected variation in response to the interventions is likely to be lower than that in a patient population, which will allow for meaningful conclusions to be drawn from a smaller sample size. Similarly, a sample size of 60 balances the need for preliminary data with the practical constraints of the logistical and financial resources of the study.

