#### Statistical Analysis

##### Overview

The modified intention-to-treat principle will guide the analysis for all outcomes within the full analysis set. Quantitative data will be summarized using mean, SD, minimum, maximum, and median values. Enumeration data will be presented as frequency and the corresponding percentage. Intragroup comparisons will be conducted using the Student paired *t* test or Wilcoxon signed rank test for continuous variables and the chi-square test for categorical variables. Intergroup comparisons will be conducted using the independent-sample *t* test or the Mann-Whitney *U* test. Significance thresholds will be set at *P*<.05 for all 2-tailed tests.

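### The stated power above 80% does not follow from the inputs given for it (d=0.6, 30 per group, voxel P<.001 with cluster-level FWE P<.05)

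*Protocol article*

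**What the plan says.** Power Analysis reports an a priori calculation with G*Power and the fMRIPower toolbox. Its inputs are an effect size ("an expected effect size of Cohen *d*=0.6 (moderate) was used"), an inference procedure ("For a voxel-level threshold of *P*<.001, uncorrected and cluster-level FWE of *P*<.05") and 30 per group. Its result is that with "a sample size of 30 per group, the analysis achieves >80% power to detect activation differences in relevant cortical regions". It adds: "This power analysis informed our sample size and statistical thresholds". It does not name the test, the contrast, the sidedness, the assumed extent of activation or the image smoothness.

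The surrounding text points to a two-group, two-sided comparison:
- The Interventions section has "participants allocated in a 1:1 ratio to the intervention and control groups".
- The statistical Overview says "Intergroup comparisons will be conducted using the independent-sample *t* test or the Mann-Whitney *U* test" and "Significance thresholds will be set at *P*<.05 for all 2-tailed tests".
- fMRI Data Analysis describes its aim as the difference in response between the groups.

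The Objectives section, by contrast, frames the hypothesis as change from baseline.

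The Sample Size section says that "a sample size of 60 (30 per group) is considered appropriate to achieve the study objectives". Its reasons are the exploratory aim, feasibility, resources and the lower variation expected in healthy volunteers. It gives no power figure.

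**The concern.** The power claim concerns the primary outcome, and its main inputs are printed, so it can be checked. A moderate standardised difference with 30 per group falls short of 80% power for one ordinary two-group test at .05. It is therefore surprising to see more than 80% claimed at a threshold fifty times stricter (.05/.001 = 50).

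Two things are at stake. Readers may judge negative maps against a power that the article has not shown. The Sample Size and Future Directions sections also say that the results will inform larger trials, whose planners could carry forward an optimistic view of what 30 per group can detect.

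**Working it through.** **Inputs.** From Power Analysis: d = 0.6, n = 30 per group, voxel threshold .001 and stated power above 80%. From the statistical Overview: two-tailed tests at .05 and an independent-sample t test between groups. From Interventions: 1:1 allocation.

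**Two-group t test.** Power comes from the noncentral t distribution with df = 2n − 2 = 58 and noncentrality d·√(n/2) = 0.6 × √15 = 2.32.

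| Threshold | Two-sided | One-sided |
|---|---|---|
| .05 | 63% | 74% |
| .01 | 37.5% | 48% |
| .001 | 14% | 19.5% |

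The critical values make the pattern clear. At two-sided .05 the statistic must exceed 2.00, below the noncentrality of 2.32. At two-sided .001 it must exceed 3.47, well above it.

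**Paired test within one group.** Here df = 29 and the noncentrality is d·√n = 0.6 × √30 = 3.29, reading d = 0.6 as the mean change divided by the SD of the change.

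| Threshold | Two-sided | One-sided |
|---|---|---|
| .05 | 89% | 94% |
| .001 | 38% | 47% |

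**Attempt to reproduce more than 80%.** At the stated .001, neither table gets there. The paired test passes 80% at .05, but that is not the stated threshold.

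**What the two-group test would need, two-sided.**
- 80% power at d = 0.6: 45 per group at .05, or 98 per group at .001.
- 80% power with 30 per group: d of about 0.74 at .05, or about 1.12 at .001.

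**Cluster-level procedure.** The .001 threshold only forms clusters; significance is then judged by cluster size. The single-voxel results at .001 are therefore not the power of the stated procedure. Two rough simulations looked at that directly. Both assumed d = 0.6 uniform within a sphere, 4 mm voxels, about 28,000 voxels in the mask, and a one-sided .001 cluster-forming threshold.
- The first used about 215 null maps and 120 to 141 signal maps per setting. Power ran from 11% (8 mm radius, 12 mm smoothness) to 82% (12 mm radius, 8 mm smoothness).
- The second used 100 null and 40 signal maps per setting, all at 8 mm smoothness. Power was 25%, 70%, 95% and 100% for radii of 8, 12, 16 and 20 mm.

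At the one setting singled out in both (12 mm radius, 8 mm smoothness) they gave 82% and 70%, which shows how rough they are. They agree that the answer depends on extent, and the first also varied smoothness. The power statement gives neither quantity.

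**The case against.** The strongest reply is that the claim is about cluster inference in relevant regions, not about one voxel, and that cluster inference can exceed 80% at d = 0.6 with 30 per group. That stands. A reader might infer from the 14% that the true power is 14%, or that the whole-brain analyses are shown to be unpowered. The article does not support either reading: Multiple-Comparison Correction calls .001 an initial threshold, and the simulations pass 80% for large, uniform regions. What remains is that the result cannot be obtained from the inputs printed beside it.

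A second reply is that the contrast may be within-group. The hypothesis is framed against baseline, and the immediate post-procedure scan exists only in the intervention group, so that component of the primary outcome can only be within-group. This is fair, but a paired test has 38% single-voxel power at .001 (47% one-sided). It reaches 89% only by moving to .05.

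A third reply is that adjustment for baseline would help. With assumed baseline correlations of 0.3 to 0.8, ANCOVA gives 17% to 66% at two-sided .001. At two-sided .05 it passes 80% only from a correlation of about 0.6. The power statement mentions neither the adjustment nor a correlation.

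A fourth reply is that pilot data, toolbox output and region definitions may sit in a fuller document. They may, and an article need not print them all. But the article does print a definite result with selected inputs, and as printed the two do not connect.

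Finally, the two accounts of the sample size do not flatly contradict each other. Sample Size does not rest on feasibility alone, and Power Analysis says that the calculation informed the number, not that it fixed it. The gap is that one section gives reasons without power, while the other credits a power calculation that the first never mentions. That the study is exploratory, and lists its small sample as a limitation, softens the consequence. It does not make the figure right: the limitation disclaims power only for clinical efficacy.

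**Conclusion.** The point holds in this form: power above 80% does not follow from d = 0.6, 30 per group, voxel P<.001 and cluster-level FWE P<.05. For the simplest test that the text supports, one two-group regional contrast at two-sided .05, power is 63% (74% one-sided), before any correction across regions, tasks or time points. Single-voxel power at the cluster-forming threshold is 14% two-group and 38% paired. For the full cluster procedure the figure is indeterminate from the article: about 11% to above 80% in rough simulations, with the upper end needing a large region of uniform effect.

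The t-test results assume normal data, equal variances, all 30 per group analysed, and d expressed in the SD of the quantity tested. The simulations assume spherical, uniform effects and carry visible sampling error.

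It would go too far to say that the design cannot reach 80% under any cluster model, or that the article intends null maps to be read as no effect. It says neither.

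**What to change.** Keep 60 participants. Replace the sentence claiming more than 80% with the power that the design supports, for example:

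> With 30 participants per group, a single between-group regional contrast at two-sided .05 has 63% power for d = 0.6 and 80% power for d = 0.74. Whole-brain voxelwise analyses are exploratory.

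The article does not single out such a contrast, so the sponsor should name the region, measure and time point to which the sentence refers.

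Keep a cluster-level figure only if its test, contrast, assumed extent and smoothness are stated and reproduce it. It should also use the voxel threshold that will be applied, since fMRI Data Analysis gives P<.01 with cluster-level FDR whereas Power Analysis and Multiple-Comparison Correction give P<.001 with cluster-level FWE.

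Make Sample Size and Power Analysis give the same basis for 60: either the exploratory and practical reasons, with the power reported as what that number provides, or a calculation that leads to it.

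The cost is rewording plus the choice of one contrast; recruitment and scanning do not change. The downside is a less favourable stated power.

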##### Correlation of Clinical Outcomes and fMRI Data

Associations between clinical measures and fMRI-derived metrics (amplitude of low-frequency fluctuation, functional connectivity, and network strength) will be assessed using partial Pearson correlations controlling for age and sex. Given the multiple regions and measures assessed, the Benjamini-Hochberg FDR correction (*q*<0.05) will be applied to adjust for multiple testing across correlations. In addition, exploratory Spearman correlations will be performed to confirm the robustness of the observed associations.

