##### fMRI Data Analysis

The fMRI data will undergo preprocessing using either the Data Processing and Analysis for Brain Imaging or CONN toolboxes, which will encompass essential steps such as slice timing correction, realignment for motion correction, regression to remove confounding effects, normalization to a standard template, smoothing to enhance signal-to-noise ratio, detrending to remove low-frequency drifts, and filtering to focus on relevant frequency bands, aligning with established practices in the field. After data preprocessing, amplitude of low-frequency fluctuation, functional connectivity, and large-scale functional brain network analysis will be conducted to investigate the difference in neurophysiological responses between the groups. The results will be interpreted in the context of the experimental paradigm to elucidate neural correlates of the studied phenomena, providing insights into the effects of *nasya karma* on brain function. Voxels exhibiting expected time-course correlations (30-second periods) will receive high activation scores, whereas those showing no correlation or deactivation will receive lower or negative scores, respectively. MRI data analysis will use general linear models via statistical parametric mapping (SPM). fMRI data will be processed using MATLAB 2023 (MathWorks Inc).

Resting phase MRI data will be analyzed using software tools such as SPM, the CONN toolbox, and the Functional Magnetic Resonance Imaging of the Brain Software Library (Analysis Group), whereas task phase fMRI will specifically use SPM. Given the focus on group data in this study, complex patterns of brain activation will be interpreted collectively rather than individually. For voxel-based analysis, a significance threshold of *P*<.01 at the voxel level and *P*<.05 corrected for false discovery rate (FDR) at the cluster level will be applied. Connectome-based analysis will use a threshold of *P*<.05 corrected for FDR. Additionally, Pearson correlation analysis will be performed to explore potential associations between clinical outcomes and fMRI findings, examining changes in brain activity following different interventions.

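### If both arms are pooled, the brain-clinical correlations adjust for age and sex but not for arm, so arm effects on both measures can create or hide a correlation

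*Protocol article*

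**What the plan says.** The section Correlation of Clinical Outcomes and fMRI Data says that associations between clinical measures and three imaging metrics (low-frequency amplitude, connectivity, network strength) "will be assessed using partial Pearson correlations controlling for age and sex". It adds that "the Benjamini-Hochberg FDR correction (*q*<0.05) will be applied to adjust for multiple testing across correlations", and that "exploratory Spearman correlations will be performed to confirm the robustness of the observed associations". No arm term, stratification or within-arm correlation is mentioned.

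The section fMRI Data Analysis introduces the same analysis and describes it as "examining changes in brain activity following different interventions". It does not mention arm as a covariate either.

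Other relevant statements are:
- Sample Size: "a sample size of 60 (30 per group) is considered appropriate".
- Interventions: "participants allocated in a 1:1 ratio to the intervention and control groups, matched for age and sex".
- Statistical Analysis, Overview: "Significance thresholds will be set at *P*<.05 for all 2-tailed tests".

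**The concern.** A correlation computed over two pooled arms mixes two things: the association between the measures among people in the same arm, and the product of the two arm differences. Only the first says that people whose brain measure is higher also have better clinical scores. The second arises whenever both measures differ by arm, for whatever reasons.

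This design makes a shift on both sides plausible. On the imaging side, the Objectives hypothesise greater activation and connectivity after nasya karma. On the clinical side, the Blinding section blinds neither participants nor assessors, the control group receives nothing, and the outcomes include perceived stress, anxiety and quality of life, which are open to expectation. A scan metric and a questionnaire score could each move in the treated arm through separate routes.

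These correlations are the only analysis planned to connect brain measures with clinical measures, so a reader will take a significant coefficient as evidence of such a link. Adjusting for age and sex does not help, because the arms are said to be matched on both and neither can stand in for arm.

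**Working it through.** **The plan's own figure.** The article gives no expected coefficient, power or error rate for the correlations, so there is none to reproduce. Its power statement concerns activation differences and does not bear on this point.

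**Inputs.**
- From the article: 30 per arm, 1:1 allocation, two-sided 5% level, age and sex partialled out, d=0.6 for imaging activation (Power Analysis).
- Assumed: the arm shift in the clinical measure, for which the article gives no figure, and equal shifts in both measures. A range is shown.

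**Formula.** Let both measures have SD 1 within arm, arm shifts d1 and d2, and within-arm correlation ρ. With 1:1 allocation, arm contributes d1·d2/4 to the covariance and d²/4 to each variance:

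r(pooled) = (ρ + d1·d2/4) / √[(1 + d1²/4)(1 + d2²/4)]

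**No within-arm link (ρ=0), equal shifts.**
- 0.6 SD: 0.09/1.09 = 0.08
- 0.8 SD: 0.16/1.16 = 0.14
- 1.0 SD: 0.25/1.25 = 0.20

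**Rejection rates.** 20,000 simulated trials of 30+30, with age and sex partialled out, and then age, sex and arm:

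| Shift in both measures | Pooled r | Rejects at .05, age and sex | Rejects at .05, arm added | Rejects at .005, age and sex |
|---|---|---|---|---|
| 0.3 SD | 0.02 | 5.6% | 5.2% | 0.5% |
| 0.6 SD | 0.08 | 9.1% | 5.0% | 1.5% |
| 0.8 SD | 0.14 | 17.6% | 5.0% | 3.5% |
| 1.0 SD | 0.20 | 33.8% | 5.2% | 9.5% |
| 1.5 SD | 0.36 | 84.1% | 4.8% | 51.9% |

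A separate simulation of the same size gave 9.7%, 18.4% and 34.2% at 0.6, 0.8 and 1.0 SD. The .005 column is an assumed stand-in for a stricter cut-off after multiplicity correction. The true Benjamini-Hochberg cut-off depends on how many correlations are tested and on their results.

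**Only one measure shifts (0.6 and 0).** The numerator is zero, so r=0. The simulated rate is 5.2%.

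**Opposite shifts hiding a real link (ρ=0.40, d=+1 and −1).** r = (0.40 − 0.25)/1.25 = 0.12. In simulation the mean coefficient was 0.11, significant in 13% of trials. With arm in the model it was 0.40, significant in 88%.

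**The planned safeguards.** Benjamini-Hochberg limits chance findings among correlations that are truly zero, whereas here the pooled correlation is truly non-zero. A pooled Spearman coefficient without arm carries the same between-arm component, so it would tend to agree with the Pearson result.

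**The case against.** The strongest objection is that pooling is inferred. The wording "examining changes in brain activity following different interventions" could also describe correlations run separately after each intervention, and the correlation section names no analysis population. Run within arm, arm is constant and the problem disappears. This stands as a condition on the point. It does not remove it, because the article specifies the covariates, never mentions within-arm analysis, and reads most naturally as one analysis over both arms.

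Second, the size at the article's own effect is modest. At 0.6 SD on both measures about 90% of trials would show no significant coefficient, and at 1.0 SD about two thirds would not. The 0.6 belongs to imaging activation. Nothing in the article supports applying it to a clinical score, and large clinical shifts are not obvious in screened healthy volunteers. The rates are also uncorrected and per test, so the planned correction would lower them. All of this stands.

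Third, rejecting a zero pooled correlation is not strictly a type I error, because that correlation is not zero. The fault lies in interpretation, and the article claims only to explore associations. This is correct, but such a coefficient would naturally be read as a link between individuals' brain and clinical measures.

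**Conclusion.** The point holds, conditional on pooling. The specified model leaves out the one variable that the design can make a common cause of both measures. When both shift by arm, the pooled coefficient is biased as an estimate of the within-arm association, upward or downward according to the signs. With equal shifts and no within-arm link, the uncorrected per-test rejection rate is about 9-10% at 0.6 SD, 18% at 0.8 SD and 34% at 1.0 SD, against 5% with arm adjusted. These figures rest on an assumed clinical shift.

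A reader might infer that the trial will report a brain-clinical link whenever both measures differ between arms, or that the plan's own effect size implies serious inflation. The documents support neither. The article gives no clinical effect size, significance is far from assured at moderate shifts, and nothing arises if only one measure moves. Nor does the point touch the primary outcome or the between-group comparisons. It concerns a secondary exploratory analysis and is worth correcting because the correction is nearly free.

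**What to change.** In Correlation of Clinical Outcomes and fMRI Data:

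1. State whether the correlations pool the arms. If they do, partial out age, sex and arm.
2. Report the coefficient within each arm descriptively beside the adjusted one. The adjusted coefficient assumes a similar association in both arms, and with 30 per arm the separate values will be imprecise.
3. Replace the plain Spearman check with a rank-based partial correlation using the same covariates.

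The cost is one residual degree of freedom, from 60−2−2=56 to 60−2−3=55. No extra data, scans or participants are needed.

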#### Protocol Adherence Monitoring

In this study, all *nasya karma* procedures will be administered at the NARIP by trained investigators on alternate days. Participants will not perform *nasya karma* at home. This approach ensures direct procedural supervision, standardized administration, and immediate monitoring for any adverse effects or participant discomfort. Direct assessment by the investigator at each session enhances protocol adherence, fidelity, and the overall robustness of study execution, eliminating the variability associated with home-based administration and, thereby, strengthening the internal validity and reliability of the study findings as in Table 1.

**Table 1 table1:** Gantt chart.

		Week 0	Baseline		Intervention period (1st-13th day)	Follow-up	
			1st day	1st day (immediately after *nasya*)		14th day	30th day
Participant screening, including laboratory tests		✓					
Informed consent		✓					
Randomization		✓					
Intervention: *nasya karma* (group A)			✓		✓		
Control (group B): without *nasya karma*							
